#### Multiple comparisons correction

For multiple comparisons correction across metrics and modalities, the following strategies will be applied: For primary imaging endpoints, FDR correction will be implemented to control for type I error—specifically, for fMRI functional connectivity analyses, FDR correction will be applied at the ROI and brain network level, and for fNIRS prefrontal ROI activation analyses, FDR correction will be applied at the channel level or ROI level, as appropriate. For secondary imaging metrics, appropriate correction methods will be applied within each set of analyses, and findings will be interpreted with caution.

## Discussion

This protocol describes a three-arm randomized controlled trial designed to determine whether PC6 magnetic stimulation provides additional cognitive benefit when combined with standard left DLPFC rTMS in patients with post-stroke cognitive impairment, and to characterize associated network-level remodeling using combined fNIRS-fMRI. By comparing PC6 magnetic stimulation with PC6 acupuncture and sham magnetic stimulation at PC6 while holding left DLPFC rTMS constant across arms, the study aims to quantify the incremental effect of PC6 magnetic stimulation versus sham and to compare magnetic stimulation with acupuncture. The trial’s multimodal imaging framework is expected to provide mechanistic insight into how this combined “central regulation and peripheral input” strategy may reshape cognition-related networks.

Cognitive impairment after stroke has been shown to be closely related to disruptions in multiple brain network connections. Resting-state functional MRI studies have found that patients with PSCI exhibit significantly reduced local functional connectivity in cognitive-related networks, including the DMN, SN, cerebellar network, and orbitofrontal cortex, with particularly prominent impairments in the functional connectivity and nodal efficiency of the bilateral caudate nuclei (43). In other words, stroke disrupts both local and global functional connectivity, particularly damaging information transmission pathways involved in cognition, and the extent of this network damage correlates closely with cognitive deficits (44, 45). A prospective study indicated that stronger interhemispheric connectivity of the DMN during the subacute phase of stroke predicts better cognitive recovery at 6 months; conversely, overactivation of the SN may indicate poorer cognitive outcomes (46). Therefore, enhancing the integration of cognitive brain networks in PSCI patients is considered a key approach to promoting cognitive rehabilitation (47). This study targets this mechanism through magnetic stimulation of the PC6 acupoint, located on the medial forearm near the distribution of the median nerve (48). We hypothesize that magnetic stimulation of this acupoint can activate widespread central networks via sensory afferents, thereby strengthening interactions among higher-order networks such as the DMN and CEN and restoring the disrupted network balance after stroke. Concurrently, high-frequency rTMS applied to the DLPFC focuses on enhancing the executive control network, and the combination of these two interventions is expected to jointly improve brain network function at different levels.

PC6 was chosen for its dual relevance in TCM and modern neuroimaging. In TCM, cognitive disorders reflect disturbance of ‘Shen’ (spirit), and PC6 is traditionally used to calm the mind and regulate cardio-cerebral function (49). This study combines this empirical knowledge with modern technology, precisely applying magnetic stimulation to PC6 to elicit its therapeutic effects. Moreover, Neuroimaging studies have demonstrated that acupuncture at PC6 can significantly modulate neural activity in multiple brain regions, including the middle frontal gyrus, precuneus, parahippocampal gyrus, superior temporal gyrus, fusiform gyrus, anterior cingulate cortex, and thalamus (50, 51). Different acupoints exert distinct effects on brain networks, whereas other points (e.g., HT7) predominantly influence mesolimbic pathways (52), Some studies have reported improved attention and cognitive performance in stroke patients after electroacupuncture at PC6 (53). These findings objectively support PC6’s efficacy in ‘awakening the spirit and enhancing intelligence’, suggesting that stimulating this acupoint can affect brain network nodes intimately linked to cognition. Building on this, our study takes a further step by applying non-invasive magnetic stimulation to PC6, aiming to achieve similar or even stronger effects. Preliminary work with magnetic stimulation shows parallel effects, enhancing functional connectivity on fMRI and strengthening alpha-band synchrony between frontal and occipital cortices on EEG (54, 55). Therefore, if this study observes cognitive improvement in the MAG group accompanied by enhanced functional brain network connectivity, it will provide robust evidence supporting the hypothesis that acupoint magnetic stimulation enhances cognition by mediating plastic reorganization of brain networks.

This study also incorporates numerous methodological considerations aimed at enhancing the quality of evidence and the reliability of result interpretation. First, we employed a three-arm randomized controlled design, where all participants received conventional high-frequency rTMS targeting the L-DLPFC, with additional PC6 intervention introduced as a variable. This design ensures ethical compliance while attributing intergroup differences to the specific effects of either magnetic stimulation or acupuncture at PC6. Since rTMS has been demonstrated to have therapeutic benefits for PSCI (56, 57), we avoided exposing the control group to entirely ineffective treatments, thereby safeguarding patient welfare. However, it is important to acknowledge that this approach may reduce the significance of intergroup differences. To address this, we ensured sufficient statistical power through rigorous sample size estimation and balanced enrollment criteria. Second, regarding blinding procedures, we implemented both assessor and patient blinding to the greatest extent possible. Although acupuncture and magnetic stimulation differ in somatosensory perception, the sham stimulation group used a simulated coil placed over PC6 without delivering pulses, making it difficult for participants to discern whether they received actual magnetic stimulation. All clinical assessments were conducted by independent evaluators unaware of group assignments to minimize subjective bias.

Moreover, we specifically applied multimodal imaging techniques for objective efficacy evaluation. fNIRS data will be collected at three time points (baseline, immediately after the first session, and after the 15th session) to capture both acute and cumulative effects. The post-first-session scan detects rapid hemodynamic changes that reflect the immediate neuromodulatory impact of a single magnetic- or acupuncture-stimulus, consistent with rTMS-related long-term potentiation (LTP) or inhibition mechanisms (58). This immediate measurement also serves as an early indicator of whether the target brain regions respond to the intervention. The time point after 15 sessions evaluates the cumulative or sustained effects following the full course of treatment. Both neuromodulation and acupuncture may exhibit dose-dependent plasticity effects, where repeated stimulation over days or weeks leads to lasting reorganization of neural circuits and improvements in clinical outcomes (59, 60). Therefore, data collected at the end of the 15-session course can reveal long-term therapeutic effects and changes in brain networks that underlie sustained cognitive improvements. Most importantly, comparing immediate and long-term changes can distinguish transient physiological responses from enduring neuroplastic adaptations. Resting-state fMRI provides whole-brain network analysis, as well as the reconstruction of cognition-related pathways (e.g., hippocampus-posterior cingulate cortex) (61–63). If magnetic stimulation at the PC6 acupoint has a unique effect, we anticipate that fMRI will capture specific network reorganization patterns in the MAG group, such as enhanced connectivity within the DMN and between the DMN and SN, which aligns with mechanisms of post-stroke cognitive recovery. Furthermore, we plan to correlate imaging metrics with cognitive scores to examine the relationship between brain network changes and clinical outcomes, thereby deepening the understanding of the underlying mechanisms.

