**Figure 2 fig2:**
[figure not shown]
Three specific intervention methods. **(A)**, PC6 magnetic stimulation; **(B)**, PC6 localization and acupuncture at PC6; **(C)**, PC6 sham magnetic stimulation.

Across all groups, high-frequency rTMS will be administered over the L-DLPFC concurrently with each session of the assigned intervention. This protocol is designed to reflect the “central regulation + peripheral input” rehabilitation model and to ensure ethical consistency across treatment arms. In addition, all patients will receive conventional rehabilitation delivered by a multidisciplinary team in accordance with the Adult Stroke Rehabilitation Guidelines (NICE NG236) (30). This includes physical therapy, occupational therapy, and speech and language therapy, provided for at least 3 h per day, on at least 5 days per week, tailored to individual goals and needs. Rehabilitation also encompasses swallowing assessment and management, prevention of complications, and support for cognitive, psychological, and functional recovery, as outlined in the guideline recommendations for comprehensive stroke rehabilitation. We will document the type, frequency, and duration of conventional rehabilitation received by each participant. If a specific intervention within conventional rehabilitation is likely to influence a patient’s cognitive level, the investigator will document its type, duration, and intensity in detail in the Case Report Form form. Therefore, we will systematically document lesion side (left/right) and key lesion features (e.g., location and volume where available).

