### Statistical analysis

#### Clinical data analysis

All analyses will be performed using SPSS 26.0 (IBM, Armonk, NY, USA) with two-tailed tests (*p* < 0.05). Quantitative data will be expressed as mean ± standard deviation. Within-group comparisons will use paired t-tests. Between-group comparisons will employ one-way ANOVA or nonparametric rank-sum tests (Kruskal-Wallis test), depending on data distribution. Count data will be presented as numbers (percentages), to be analyzed by *χ*^2^ tests, Fisher’s exact tests, or Ridit analysis. Repeated-measures ANOVA with Greenhouse–Geisser correction will be applied to evaluate longitudinal changes across timepoints. Both intention-to-treat (ITT) and per-protocol (PP) analyses will be conducted. In the ITT analysis, missing outcome data will be handled using multiple imputation under the assumption of missing at random. For the primary outcome (MoCA), we will report effect sizes and 95% confidence intervals for between-group differences in score changes. Clinical relevance will be interpreted using published MoCA change ranges and distribution-based benchmarks, rather than a prespecified minimal clinically important difference (MCID). Pearson’s or Spearman’s correlation coefficients (selected based on data distribution) will be calculated to examine associations between clinical scales and neuroimaging parameters. Covariates including age, sex, years of education, time from stroke onset to study enrollment, and a quantitative metric capturing the “dose” of conventional rehabilitation (derived from documented type, frequency, and duration), and lesion side (left/right) will be incorporated into a multivariate linear regression model evaluating the primary endpoint (change in MoCA score) and key secondary cognitive outcomes. Furthermore, to explore the potential modifying effect of lesion side on treatment response, we will conduct an exploratory analysis by adding a Group × Lesion Side interaction term to the primary multivariate model for the MoCA change score and key imaging outcomes. These interaction analyses will be explicitly labeled as exploratory, and their results will be interpreted cautiously due to the limited statistical power for detecting interaction effects.

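### The Discussion would accept improvement in the MAG arm plus enhanced connectivity, with no reference to sham, as robust evidence that PC6 stimulation works through network reorganization

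*Protocol article*

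**What the plan says.** In the Discussion of the protocol article, the paragraph on the choice of PC6 ends with a statement of what result would support the mechanism: "if this study observes cognitive improvement in the MAG group accompanied by enhanced functional brain network connectivity, it will provide robust evidence". The hypothesis this evidence is meant to support is that "acupoint magnetic stimulation enhances cognition by mediating plastic reorganization of brain networks". The condition concerns the MAG group only; neither SHM nor ACU is mentioned.

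The rest of the article describes what all three arms have in common:

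- Intervention and grouping: "Across all groups, high-frequency rTMS will be administered over the L-DLPFC concurrently with each session of the assigned intervention". Conventional rehabilitation is also given to all patients, "provided for at least 3 h per day, on at least 5 days per week, tailored to individual goals and needs", and it includes support for cognitive recovery.
- Discussion, on the three-arm design: "Since rTMS has been demonstrated to have therapeutic benefits for PSCI", which is the stated reason that the control arm is not left untreated.
- Discussion, on networks: "high-frequency rTMS applied to the DLPFC focuses on enhancing the executive control network".

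On analysis, Clinical data analysis lists, as a general method, "Within-group comparisons will use paired t-tests". It also promises between-group differences in MoCA change with 95% confidence intervals, and correlations between clinical scales and imaging parameters. The fNIRS section plans a Group × Time test. The fMRI section and the multiple-comparisons section, which cover the confirmatory FC outcome, name no contrast between arms.

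**The concern.** Both halves of the condition are things the article expects from treatment that every arm receives. Cognition should improve with rTMS and daily rehabilitation, and rTMS is expected to act on a cognitive network. A patient group given only the background treatment could meet the condition, and SHM is such a group. A result that sham can also produce does not bear on PC6.

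The word *mediating* goes a step further. Two changes seen together in one arm do not show that one carries the effect of the other, and the article describes only correlations.

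What is at stake is the mechanistic conclusion. If the sentence were followed literally, the trial could report robust support for a PC6 mechanism from data compatible with no PC6 effect.

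**Working it through.** **1. The plan's own figure.** Sample size gives 99 patients (33 per group) for a one-way ANOVA with three groups, f = 0.32, α = 0.05 and power 0.80. With noncentrality λ = N·f²:

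- N = 96: λ = 96 × 0.1024 = 9.83, power 0.795.
- N = 99: λ = 99 × 0.1024 = 10.14, power 0.808.

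So 99 is reproduced. This is a test between groups; it gives no support to a reading within one arm.

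**2. What each arm is expected to show if PC6 stimulation adds nothing.**

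| Component | MAG | SHM | Expected effect according to the article |
|---|---|---|---|
| L-DLPFC rTMS at each session | yes | yes | benefits PSCI; acts on the executive control network |
| Rehabilitation, at least 3 h/day, 5 days/week | yes | yes | includes support for cognitive recovery |
| Active PC6 magnetic stimulation | yes | no | the question of the trial |

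The first two rows are enough to produce improvement with a network change in MAG. They are the same in SHM and cancel in the MAG-minus-SHM difference.

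**3. How often the within-arm pattern would appear with zero PC6 effect.** The sentence defines no test, so this step reads it as two significant within-arm changes in the favourable direction. Inputs: n = 33 (Sample size) and two-sided α = 0.05. The background gain dz, in SD of the change score, is not in the document and is shown as a range.

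The test statistic has a noncentral t distribution with 32 degrees of freedom and noncentrality dz·√33 = 5.745·dz. The critical value is 2.037. For two independent measures with the same dz, the joint probability is p².

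| Assumed dz | Noncentrality | p, MoCA alone | p², MoCA and connectivity |
|---|---|---|---|
| 0.3 | 1.72 | 0.387 | 0.15 |
| 0.5 | 2.87 | 0.795 | 0.63 |
| 0.8 | 4.60 | 0.994 | 0.99 |

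If the two changes are positively correlated, the joint probability lies between p² and p: 0.15 to 0.39, 0.63 to 0.80, and about 0.99. The FDR correction planned for connectivity is not modelled and would lower these figures.

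**4. The between-group contrast under the same conditions.** With equal background gain in MAG and SHM, the expected difference is zero whatever dz is. A two-sided 0.05 test then favours MAG with probability 0.025 per measure. Requiring both, under independence, gives 0.025² = 0.0006.

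**The case against.** The best defence is that this is one loose sentence in a Discussion whose logic is otherwise right. The Introduction words the hypothesis against the control intervention, for cognition and for network change. The Discussion opens with the incremental effect over sham and later attributes effects to differences between groups. It also admits that giving rTMS to everyone may shrink those differences. The primary outcome is reported as between-group differences in change, fNIRS has a Group × Time test, and the sizing is between groups. All of this stands, and it limits the point to interpretation.

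Four stronger readings are tempting and are not supported:

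- **That the sentence is an operative decision rule.** It sets no test, threshold or analysis set. It is an advance statement of how a result would be interpreted.
- **That the paired t-tests are the planned test of the mechanism.** They are listed as a general method for clinical data and are nowhere tied to this sentence. The imaging sections do not mention them.
- **That 0.80 at dz = 0.5 is a false-positive rate to set against 5%.** If patients truly improve by 0.5 SD, the paired test is right to reject no change, so the figure is power. The error arises only when the change is attributed to PC6. MoCA alone is also only half of the stated condition.
- **That natural recovery and repeat testing are documented sources of gain.** They are plausible, but the article does not describe them as such, and the argument does not need them.

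The defence does not cover the confirmatory FC outcome. The mechanistic claim leans on it most, and the sections on its analysis state no comparison between arms. Nor does it remove the word *mediating*, since only associations are planned.

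**Conclusion.** The point holds as a fault of interpretation. The Discussion would treat a pattern in MAG alone as robust evidence for a mediated PC6 effect, although the article itself expects the shared treatment to improve cognition and to act on a cognitive network. This departs from the article's own between-group reasoning.

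Under zero PC6 effect, the pattern read as two significant within-arm changes would occur with probability about 0.15, 0.63 or 0.99. This assumes background gains of 0.3, 0.5 or 0.8 SD, 33 patients, equal and independent gains on both measures, and no FDR correction. The size therefore depends on a gain that the document does not give. That sham could meet the same condition depends on none of these numbers.

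A reader might infer that the design or the primary result is compromised. It is not: the primary between-group MoCA analysis and the sample size stand.

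**What to change.** - In the Discussion, make the mechanistic conclusion conditional on MAG-minus-SHM differences in both MoCA change and change in the primary FC outcome.
- In the section on fMRI processing and analysis, state the MAG-versus-SHM contrast in change for FC.
- In Clinical data analysis, say that within-group paired tests are descriptive and are not evidence for PC6. Whether to print their p-values is a reporting preference.
- Describe FC–MoCA correlations as associations, and drop *mediating* from the conclusion.

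The cost is wording, with no new data and no change to sample size or primary analysis. The downside for the investigators is a narrower mechanistic claim. The change should be made before results are known.

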## Limitations

This single-center exploratory trial has several limitations. Firstly, although the L-DLPFC was selected as the target region, target localization was implemented via cap-based approaches (the “5-cm rule”) rather than neuronavigation techniques. Previous studies have demonstrated the imprecision of the “5-cm rule” for rTMS stereotactic localization, with evidence showing that this method may result in stimulation over non-prefrontal regions in a substantial proportion of subjects (64–66). This cap-based approach may therefore induce inter-individual localization variability and potentially compromise the internal validity of the trial. Secondly, clinical heterogeneity in PSCI may still influence treatment response. While key factors such as stroke subtype, lesion characteristics, and time from stroke onset to enrollment will be documented and explored as covariates in multivariable and sensitivity analyses, the trial may be not powered for definitive subgroup analyses. Thirdly, the use of a single acupoint (PC6, Neiguan) enhanced the rigor of experimental control, yet it deviates from routine clinical practice where multi-acupoint acupuncture is the standard modality. Thus, extrapolation of the study results to real-world settings should be performed with caution. Fourthly, despite efforts to optimize masking, blinding may be imperfect due to the distinct somatosensory experiences between acupuncture and magnetic stimulation, which may introduce expectation-related bias. Finally, the follow-up duration is relatively short, which limits conclusions regarding the long-term durability of cognitive and network-level changes; larger multicenter trials with longer follow-up will be necessary to confirm sustained clinical benefits.

## Conclusion

This trial will provide the first RCT evidence on the cognitive benefits and network-level mechanisms of combining PC6 magnetic stimulation with standard left DLPFC rTMS for PSCI, using fNIRS–fMRI. Positive results would support a practical, non-pharmacological rehabilitation strategy and inform subsequent large-scale, multicentre trials in acupoint-based neuromodulation.
